### Recruitment

Patients are screened in the transplant assessment clinic and are provided with the trial Patient Information Sheet (PIS) directly or by post. The trial is then discussed with a team member in depth at the time of the subsequent short-stay inpatient assessment. Informed consent is then obtained by a member of the research team and a baseline quality of life (QoL) assessment is performed.

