### Intervention

The trial intervention period will commence when the patient arrives on the ICU following transplant surgery and will continue for 12 h postoperatively. In both study groups (GDFT and control), a FloTrac sensor (EV1000 Clinical Platform, Edwards Life Sciences, Irvine, CA, USA) will be used to measure SV and cardiac output. In the GDFT group only, this information will be used to guide IV fluid therapy according to the study protocol (Fig. 3). The intervention consists of an initial bolus infusion of 250 mL Hartmann’s on arrival to ICU. If this leads to a > 10% increase in SV the patient is deemed to be fluid responsive and the bolus is repeated until no further SV response is achieved (i.e. euvolaemia). SV is continuously monitored and the bolus is repeated if the SV drops by 10%. There are no extra maintenance fluids in those who are not fluid responsive.

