### Outcome measures

The primary outcome of this study is feasibility. A recruitment rate of greater than 40% of patients fulfilling the criteria for this study will be deemed successful. We shall assess patient recruitment, clinician support for the trial, completion rate of the intervention and reasons for participant withdrawal from the trial. Secondary outcomes will explore the safety of the intervention, and to assess endpoints in order to determine the most appropriate endpoints for a future trial of efficacy, and to facilitate sample size calculation. All transplant-related and other complications will be recorded throughout the inpatient stay as well as at 3 and 6 months’ follow-up. To monitor safety, complications likely to be related to the intervention will be reported and reviewed as a potential serious adverse event (SAE). The safety profile and complication rates in both arms (blinded) will be reviewed regularly by an external Data Monitoring Committee (DMC). Most studies evaluating the benefit of GDFT choose length of hospital stay or incidence of postoperative complications as endpoints. In the high-risk scenario of liver transplantation, long-term graft (transplanted liver) function and patient survival may be more appropriate endpoints. However, as the outcomes of liver transplantation continually improve, these endpoints may not be achievable and other clinically relevant endpoints, such as number and severity of complications or health-related quality of life (QoL), may be more appropriate.

A recent liver transplant patient and public involvement (PPI) forum held at the Royal Free Hospital sought the views of liver transplantation patients regarding the most important outcome measures in liver transplant research. Health-related QoL was deemed to be the primary endpoint which was most useful in liver transplant trials. A composite measure of QoL and survival called quality-adjusted life years (QALYs) will be calculated in the study. QoL will be measured using the EuroQol five dimensions, five levels (EQ-5D-5 L) questionnaire which is recommended by NICE to inform cost-utility analyses of healthcare interventions [22].

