### Data collection and analysis

Each participant will be given a unique trial Participant Identification Number (PIN). The health-related QoL (EQ-5D-5 L questionnaire) will be collected at the baseline, hospital discharge and at 3 and 6 months’ follow-up. Utility value will be estimated from the EQ-5D-5 L data at different time points using the crosswalk algorithm developed by van Hout [23], which maps EQ-5D-5 L responses to an EQ-5D-3 L UK value set, as per the new NICE position statement and NICE reference case [23–25]. Continuous haemodynamic data from the FloTrac device will be collected during the study period for both arms of the study as well as intraoperative and postoperative IV fluid infusions (including IV fluids, inotropes, vasopressors and transfusions of blood and blood products). The volumes and timings of IV fluid boluses according to the SV changes will also be recorded in the GDFT arm. Complications will be recorded and graded according to Clavien-Dindo classification along with treatment costs [26].

The two treatment groups will be compared to ensure that they have similar baseline characteristics including cirrhosis aetiology using means and standard deviations or medians and inter-quartile ranges for continuous variables, as appropriate, and frequency counts and percentages for categorical variables. Information on donor characteristics (DBD or DCD), warm/cold ischaemia times, operative and reperfusion timing as well as technique of transplantation will also be collected and compared.

For feasibility outcomes, the proportion of patients who consent to be randomised will be presented with a 95% confidence interval. The proportion of patients withdrawn from GDFT will be presented, as well as the proportion of patients who deviate from the GDFT protocol for the 12-h intervention period.

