All complications will be documented and graded by the Clavien-Dindo classification system. The mean difference in the proportion of people with a complication between the two groups will be calculated and the difference between those with a mild (Clavien-Dindo grades 1–3) versus severe (Clavien-Dindo grades 4 and 5) will be assessed. A 95% confidence interval will be presented. The median number of complications and the median grade of complications in each group will be presented. The median length of stay in ICU and in hospital will be presented for each group. The rate of readmission to ICU will also be presented for each group. Quality of life scores will be summarised for each group using mean profile plots over time. The mean difference in QoL scores between the two groups at 12 h will be presented with a 95% confidence. If the data is not normal, a median difference will be presented.

Kaplan-Meier plots will be presented to compare survival rates between the two groups.

All other secondary outcomes will be summarised for each group using mean profile plots over time. For binary secondary outcomes, the mean difference in proportion at 12 h between the two groups will be presented with 95% confidence intervals. For continuous secondary outcomes, mean/median differences at 12 h will be presented as appropriate, with 95% confidence intervals.

The results will inform us how sensitive the outcome measures are and, along with other information, will be presented to a focus group involving liver transplant patients and their carers, the COLT trial team, a group of transplant surgeons and physicians not involved with the trial and other major stakeholders including representatives of specialist societies. The results of the focus group will be used to determine the primary outcome of a subsequent multicentre RCT aimed at determining the efficacy of GDFT in liver transplantation and the costs involved. The results will also inform a sample size calculation to determine the number of patients required for the primary outcome chosen.

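### The between-group quality-of-life difference is set at 12 h, but EQ-5D-5L is not collected then, so the stated contrast cannot be computed

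*Protocol article*

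**What the plan says.** All of the following is in the Methods of the protocol article.

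- **Collection of quality of life.** Under Data collection and analysis, the EQ-5D-5L "will be collected at the baseline, hospital discharge and at 3 and 6 months’ follow-up". The Recruitment section fixes when baseline is taken: "Informed consent is then obtained by a member of the research team and a baseline quality of life (QoL) assessment is performed". That happens during pre-transplant assessment.
- **Analysis of quality of life.** Later in Data collection and analysis, scores are to be summarised by group in mean profile plots over time, and then: "The mean difference in QoL scores between the two groups at 12 h will be presented", with a 95% confidence interval. A median difference replaces the mean if the data are not normal.
- **What 12 h denotes.** Under Intervention, the trial intervention period "will commence when the patient arrives on the ICU following transplant surgery and will continue for 12 h postoperatively".
- **Other secondary outcomes.** Complications, length of stay, ICU readmission and survival each get their own summary, with no 12 h limit. A further paragraph then deals with all remaining secondary outcomes. It includes the sentence "For binary secondary outcomes, the mean difference in proportion at 12 h between the two groups will be presented with 95% confidence intervals" and a parallel one for continuous outcomes, also at 12 h.
- **Collection of complications.** Under Outcome measures: "All transplant-related and other complications will be recorded throughout the inpatient stay as well as at 3 and 6 months".

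**The concern.** The analysis time and the collection times for quality of life do not meet. Twelve hours is the end of the intervention period, and it appears to have been carried over into a sentence about an outcome first measured after randomisation at hospital discharge. An analyst following the text would find no data for the contrast and would have to pick another time.

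This matters because the Outcome measures section reports that the patient forum regarded health-related quality of life as the most useful primary endpoint for liver transplant trials. The results are also meant to show how sensitive the candidate outcomes are, to go to a focus group that settles the next trial's primary outcome, and to inform its sample size. If the time point is chosen only once the data are in, from discharge, 3 months and 6 months, the choice for a leading candidate endpoint could follow the results.

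A smaller concern sits beside it. The two 12 h sentences for binary and continuous secondary outcomes do not repeat the limitation to the remaining outcomes that opens their paragraph. Taken alone, they could be applied to outcomes for which 12 h makes no sense.

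**Working it through.** The plan gives no numerical figure to reproduce here; the article says that no power calculation is required. The check sets the stated times side by side.

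**1. Overlap of analysis and collection times for quality of life**

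| Scheduled EQ-5D-5L assessment | Position relative to 12 h after ICU arrival |
|---|---|
| Baseline | At consent, before surgery and randomisation |
| Hospital discharge | After the ICU stay; see step 2 |
| 3 months | Later |
| 6 months | Later |

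Assessments at 12 h: 0 of 4. Patients with a score available for the 12 h contrast: 0 of 50 (25 per arm, from the Power calculation section). The switch to a median difference does not help, because it would need the same absent scores.

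**2. How far 12 h is from the first post-randomisation score**

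The Discussion gives the centre's historical medians (1999 to 2008): hospital stay of 33 days with a complication and 21 days without, and ICU stay of 3 and 2 days respectively. These are used as a rough guide to the timing of discharge in this trial, which is an assumption.

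- Hospital stay: 21 × 24 = 504 h and 33 × 24 = 792 h.
- Ratio to 12 h: 504 / 12 = 42 and 792 / 12 = 66.
- ICU stay: 2 × 24 = 48 h and 3 × 24 = 72 h, so a typical patient is still in ICU at 12 h.

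The first usable score therefore comes some 42 to 66 times later than the stated analysis time. No plausible visit window would make a discharge score count as a 12 h score.

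**3. Scope of the 12 h rule for other outcomes**

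| Outcome | Summary given in Data collection and analysis | Tied to 12 h? |
|---|---|---|
| Complications | Difference in proportions with interval; mild versus severe; median number and grade | No; no time stated |
| ICU and hospital stay | Medians | No |
| ICU readmission | Rate | No |
| Survival | Kaplan-Meier plots | No |
| Quality of life | Profile plots; difference with interval | The difference is; the plots are not |
| Remaining secondary outcomes | Profile plots; differences with interval | The differences are |

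The natural reading is that the general 12 h rule covers only the last row. Some data do exist at that time: FloTrac haemodynamics are recorded continuously in both arms during the study period, and fluid infusions are recorded as well. The article does not say when liver function is measured.

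**The case against.** The strongest reply is that this is one misplaced time point in a secondary, estimation-only comparison within a feasibility trial. The primary outcome is feasibility. Progression depends on recruitment and on complication rates, and no sample size rests on quality of life. Nor is quality of life lost: the profile plots use the collected visits, and a between-group difference in QALYs is to be assessed. All of this stands, and it lowers the severity. It does not rescue the sentence, which specifies an analysis that has no data.

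It could also be said that a full protocol, an analysis plan or the schedule figure, none of which is shown, may settle the matter. Those could correct the time point. But this is not a detail left out of a condensed article: the article states both the collection times and the analysis time, and they conflict.

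A reader might go further and infer that every secondary comparison is set at 12 h, so that complications and survival would be compared when almost nothing has happened. The text does not support that. Those outcomes have their own summaries without a 12 h limit, and the general rule comes in the paragraph on the remaining outcomes. Nor can a 12 h comparison of liver function be called empty when its measurement times are not given. What survives is an ambiguity: the binary and continuous sentences do not restate their limited scope.

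**Conclusion.** Wrong as written, and it should be fixed. The between-group difference in quality-of-life scores at 12 h cannot be computed, because none of the four scheduled assessments falls there and 0 of 50 patients would have a score. This conclusion rests only on the collection times that the article states; the historical lengths of stay show the size of the gap and are not needed for it.

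The consequence is that the one contrast of quality-of-life scores with a stated interval has no valid time point, in a trial intended to inform the choice of endpoint and the sample size of the next one. The consequence does not reach the primary outcome, the progression rules, the data to be collected or the other planned summaries of quality of life. The loose scope of the 12 h rule for binary and continuous outcomes is a matter of wording and not a second impossible analysis.

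**What to change.** 1. In the quality-of-life sentence, replace 12 h with collected follow-up times. Differences at 3 and 6 months with 95% confidence intervals would serve, with one of them named in advance as the main time point. Six months is a reasonable choice, but what matters is that it is fixed before the data are seen. Discharge scores are better kept descriptive, since discharge falls at a different time for each patient.
2. In the binary and continuous sentences, restrict the 12 h comparison to outcomes actually measured at 12 h, such as haemodynamics and fluid volumes, and liver function if it is measured then. Say explicitly that the rule does not apply to complications, length of stay, ICU readmission or survival.
3. While editing, state the time window for the complication contrast, which currently has none.

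The cost is one revised paragraph in the protocol or analysis plan. The EQ-5D-5L and complication data are already scheduled at 3 and 6 months, so no new visits, questionnaires or patients are needed.

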### Dissemination

The results of this study will be presented to the British Transplant Society and prepared for publication in peer-reviewed journals with an interest in critical care and organ transplantation.

## Discussion

Every year 6000 to 7000 people in the UK, many of whom are in the prime of life, die from chronic liver disease which can be effectively treated with liver transplantation. However, with an increasing number of liver transplants being performed each year and a concomitant lack of suitable donor organs, transplant centres are using livers of marginal suitability. This is associated with an increased risk of postoperative complications along with reduced graft and patient survival. More than 800 liver transplants are performed per year in the UK, at a cost of approximately £80,000 per procedure. A large part of this substantial cost is due to the treatment of postoperative complications. There is consequently a major clinical and financial imperative in the NHS to reduce the complications post liver transplantation. The 1-year mortality following liver transplantation in the UK is 8.8% [27].

A recent analysis was carried out of complications following liver transplant at the Royal Free London NHS Foundation Trust. Of 551 patients who underwent liver transplantation from 1999 to 2008, 371 (67%) developed at least one significant postoperative complication. Those patients who developed a complication had a longer ICU stay (median of 3 versus 2 days) and longer hospital length of stay (median of 33 versus 21 days) than those who did not develop complications. Graft (transplanted liver) failure and mortality at 3 months postoperatively were also significantly higher in those with complications. In a more detailed recent audit from January 2011 to July 2012, data on 98 patients was examined. In this cohort 80% of patients developed at least one significant postoperative complication, with a median of two complications per patient. This apparent increase in postoperative complications is likely to reflect an increase in the number of marginal organs now used in liver transplantation and the increasing burden of comorbidities.

Rationalising postoperative fluid therapy to prevent iatrogenic harm and complications related to hyper- and hypovolaemia, such as renal failure and pulmonary oedema (Table 1), is an effective method of decreasing postoperative complications in surgical patients [28]. A goal-directed approach to fluid therapy using haemodynamic monitoring appears to have promising results in numerous randomised trials for elective and emergency surgical patients [29]. Patients with cirrhosis undergoing liver transplantation differ from the general surgical population in several ways which makes them a unique subset of patients.

Firstly, the disease process of cirrhosis entails a complex neuro-endocrine and hormonal activation, such as nitric oxide release and the renin-angiotensin system, creating a hyperdynamic circulation [30]. The haemodynamic physiology changes seen in cirrhosis (increased cardiac output, reduced systemic vascular resistance and effective central circulating blood volume) can last into the first 24-h period after liver transplantation [31]. This renders accurate assessment of intravascular volume status an exceptionally difficult task. The mechanism and timeline of alterations to these haemodynamic and neuro-endocrine changes after liver transplantation have not been adequately investigated. The COLT trial will provide an opportunity to study the response to fluid therapy in liver cirrhosis and investigate these underlying mechanisms.

Secondly, there are surgery-related factors influencing the patients’ haemodynamics after liver transplantation. Liver transplantation is high-risk surgery incurring huge surgical stress which is often prolonged in duration [32]. There are often pre-existing coagulation defects in cirrhotic patients with major blood loss during surgery requiring transfusion of blood and blood products and exacerbating the coagulopathy [8]. Major haemodynamic alterations are exacerbated by cross-clamping of the inferior vena cava during the transplant. Added to the surgical stress, there is the huge burden of ischaemia-reperfusion injury of the largest solid organ in the body which can affect vascular endothelial barrier function, activate inflammatory cascades and hence lead to undesired fluid shifts in the body and renal dysfunction [33]. These factors make it difficult to institute a fixed method of fluid assessment and replacement intraoperatively. Hence, in the COLT trial, the regimen of GDFT was instituted during the initial 12-h period postoperatively rather than during the operation.

There have been a number of retrospective analyses of the effect of fluid therapy on perioperative complications after liver transplantation. However, there have been no prospective randomised trials assessing GDFT post liver transplantation. Jiang et al. reported that the intra-operative fluid administration of > 100 mL/kg was associated with an increased time to extubation and length of ICU stay in a retrospective analysis of pulmonary complications post liver transplantation [34]. Another retrospective analysis of 62 patients showed that an intra-operative fluid infusion of > 9000 mL was a significant risk factor for developing postoperative respiratory complications [34]. Reydellet et al. reported, in a before and after retrospective study, that a GDFT approach for 2 days post liver transplantation results in decreased requirements for mechanical ventilation and duration of postoperative ileus [35]. The COLT trial is the first prospective RCT assessing GDFT in cirrhotic patients undergoing liver transplantation.

## Trial status

The COLT trial began recruitment in April 2017 and plans for completion of recruitment in approximately September 2017.

## Abbreviations

CO: Cardiac output
COLT: Cardiac output Optimisation following Liver Transplantation
DBD: Donor after Brain Death
DCD: Donor after Cardiac Death
DMC: Data Monitoring Committee
GDFT: Goal-directed fluid therapy
ICU: Intensive care unit
PPI: Patient and public involvement
QALYs: Quality-adjusted life years
RCT: Randomised controlled trial
RFLH: Royal Free London Hospital
SAE: Serious adverse events
SV: Stroke volume
